### Variables

The exposure to modifiable risk factors in combination with genomic data (polygenic risk score) in both cases and controls will be expressed as odds ratios (95% CI). Multiple logistic regression models will be built to adjust and determine the strength of association between demographic variables (sex, age, race), traditional risk factors (smoking, diabetes, hypertension, obesity, anxiety and depression, unhealthy diet, physical inactivity, alcohol consumption, and apolipoprotein B/A1 ratio [ApoB/ApoA1], and genetic data [PRS]. For each variable with a higher chance of CVD (significant OR), attributable risk estimate will be calculated for the genetic component (PRS) and other covariables. Fig 2 shows the Polygenic Risk Score flowchart.

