### Data analysis

#### Quantitative variables and statistical analysis

The Hardy-Weinberg genetic equilibrium test will be evaluated in the control group using the chi-square test or Fisher’s exact test. To estimate the association between genetic polymorphisms and risk of CVD, univariate and multiple unconditional logistic regression analyses will be conducted [32–36].

Initially, univariate binary logistic regression analyses will be performed. Thus, covariates with a p-value < 0.20 in univariate regression analyses will be considered in multiple logistic regression analysis with selection of variables according to the backward elimination technique [37, 38]. The selection process in the backward elimination allows the sample size to adjust and always uses the maximum available sample as the number of variables in the model drops [37]. Occasionally, covariates judged as confounding factors by the investigator may be forced into the final backward regression model.

Additional multiple logistic regression analyses may also be conducted using a variant of the Purposeful Selection algorithm described by Bursac *et al*. [38].

The assumption of linearity on the logit scale (log-odds) between each quantitative covariate and the binary response variable in binary logistic regression analysis will be evaluated with the construction of “Smoothed Scatter Plots” and the method of fractional polynomials [35–39]. When the assumption is not satisfied, quantitative covariates will be categorized for use in logistic regression using cut-off points, according to the literature, distribution tertiles or optimal cut-off obtained from the Receiver Operating Characteristic (ROC) curve, whichever is deemed most appropriate. In case of an optimal cut-off point, it will be defined as the one that maximizes the Youden index [39, 40].

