#### Estimation of population attributable risk

To characterize the study population, categorical variables will be described as counts and proportions and compared with Pearson’s chi-square test or with Fisher’s exact test [41]. Normally and asymmetrically distributed quantitative variables will be expressed as mean (standard deviation) or median (interquartile range), respectively [42]. Normality will be assessed by visually inspecting histograms and applying normality tests, if appropriate [43, 44]. Comparison of these continuous type variables will be carried out with Student’s t test for independent samples or Mann-Whitney test for non-parametric distribution [41].

All statistical analyses will follow the complete case analysis principle. All hypothesis tests will be 2-sided and p-value<0.05 considered statistically significant. Statistical data analysis will be conducted with SAS 9.4 (SAS Institute, Cary, NC).

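### A Youden cut-off found in the study's own cases and controls and tested there at an uncorrected 0.05 inflates type I error wherever it is used

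*Protocol article*

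**What the plan says.** All of this is in the protocol article.

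- **Trigger** (Quantitative variables and statistical analysis). Linearity on the logit is checked with smoothed scatter plots and fractional polynomials. Then: "When the assumption is not satisfied, quantitative covariates will be categorized for use in logistic regression using cut-off points".
- **Choice of cut** (same section). The cut-off is taken "according to the literature, distribution tertiles or optimal cut-off obtained from the Receiver Operating Characteristic (ROC) curve, whichever is deemed most appropriate". No order among the three sources is given.
- **Definition of the ROC optimum** (same section). "In case of an optimal cut-off point, it will be defined as the one that maximizes the Youden index". No external sample, hold-out half or correction for the search is mentioned. The study's cases and controls are the only data described.
- **Screen** (same section). "covariates with a p-value < 0.20 in univariate regression analyses will be considered in multiple logistic regression analysis", followed by backward elimination.
- **Test** (Estimation of population attributable risk). "All hypothesis tests will be 2-sided and p-value<0.05 considered statistically significant".
- **Use of the result** (Variables). For variables with a significant odds ratio (OR), an "attributable risk estimate will be calculated for the genetic component (PRS) and other covariables". The polygenic risk score (PRS) and the ApoB/ApoA1 ratio are both quantitative, and the rule exempts neither.

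**The concern.** The Youden cut is the result of a search over every possible threshold for the one that best separates these cases from these controls. An ordinary Wald p-value or confidence interval computed afterwards in the same people treats that threshold as if it had been given. The p-value is too small, the interval is centred on a selected estimate, and the OR is optimistic.

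Two later steps carry the error forward. The covariate passes the univariate screen too easily, and a PAR is computed because the OR is significant. The study exists to estimate a PAR for the genetic component after adjustment for other risk factors, so a selected cut can affect either the PRS or the factors beside it.

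The article also already fits fractional polynomials. It turns to categories at the point where the fitted curve would be most useful.

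**Working it through.** **Inputs.** 1,867 cases and 1,867 controls (Sample size calculation); two-sided 0.05; screen at p < 0.20; Youden maximum as the cut. The article gives no threshold for declaring linearity failed, so 0.05 and 0.20 are assumed below.

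**1. The plan's own figure.** Carrier frequency under the dominant model is 1 − 0.9² = 0.19. With OR 1.3 and 10% prevalence, carriers make up 22.87% of cases and 18.57% of non-cases. With H(p) = p ln p + (1 − p) ln(1 − p) and p̄ the mean of the two, the likelihood-ratio formula n = (1.960 + 1.282)² / {2[H(p₁) + H(p₀) − 2H(p̄)]} gives 1,866.7, that is 1,867 per group. The stated sample size reproduces and is unaffected by this point.

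**2. Null covariate cut at the Youden point.** In each simulated study the cut maximising the Youden index is found. With *a* cases and *c* controls above it, and n = 1,867 per group, z = ln[a(n − c) / ((n − a)c)] / √(1/a + 1/(n − a) + 1/c + 1/(n − c)). Reject if |z| > 1.96. Results over repeated sets of 4,000 to 10,000 null datasets:

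| Cut | Rejected at 0.05 | Passes p < 0.20 |
|---|---|---|
| Youden, direction fixed beforehand | 26-28% | 64% |
| Youden, direction chosen from data | 44-45% | 89% |
| Same, cuts within 10th-90th percentile | 43% | 88% |
| Median | 4.5-4.9% | not computed |
| Tertiles (2 df) | 4.8-5.1% | not computed |
| Youden found in one half, tested in the other | 5.1% | not computed |

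The last three rows locate the cause: cuts that do not use outcome data, or that use other people's outcome data, hold the nominal level. The null rejection rates depend only on ranks, so they apply to any continuous covariate.

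**3. Spurious effect.** With PAR = p_case × (OR − 1)/OR, the median null OR is about 1.14-1.15. The median PAR is about 5-6% (5th-95th percentile about 2.5-17% with direction free), and the mean is about 7% with direction fixed. The truth is 0.

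**4. Adding the trigger.** The Youden cut is now used only if a quadratic term is flagged; otherwise the linear test is used. A normal covariate is assumed, and direction is chosen from the data.

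- Flag at 0.05: 5.08% flagged × 76.7% rejected = 3.9%. Unflagged covariates add 4.4%. Total 8.3%.
- Flag at 0.20: 19.37% × 64.0% = 12.4%. Unflagged covariates add 3.7%. Total 16.1%.
- Direction fixed: 7.0% and 11% overall.

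The average over all null covariates is thus about 7-16%. Among flagged null covariates, the ones the rule covers, rejection is about 37-78%.

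**5. Covariates with a real effect.** Two assumed curves were used. For a quadratic log-odds, mean PAR was 0.215 at the lower tertile, 0.208 at the median, 0.19 at the upper tertile, 0.11 at the 90th percentile and 0.19 at the Youden cut. The Youden value ranged over 0.14-0.27 in 30 repeat samples. For a threshold curve, mean PAR ran from 0.10 to 0.145 across cuts, and the Youden value over 0.11-0.18. Mid-range cuts differ modestly on average; the Youden PAR moves appreciably from sample to sample.

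**The case against.** **The branch is conditional, and this stands.** Youden is one of three options, literature cut-offs are listed first, and tertiles ignore case status. A null covariate has a flat, hence linear, logit and reaches this branch only through a false alarm. A reader might infer that the whole analysis runs at 26-45% error, or that all its 5% tests and 95% intervals are invalid. The text does not support that: those rates apply only where linearity is judged to fail and the Youden option is taken.

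**Strong risk factors would be significant anyway.** This also stands. Several listed factors (smoking, diabetes, hypertension) are moreover diagnoses or habits. For strong quantitative factors the harm is optimism in the OR and PAR more than false positives.

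**The PRS result.** A reader might infer that the rule lets the data set the headline genetic PAR. For a score with an assumed OR of 1.3 per SD, the PAR is 33% with the lowest fifth as reference, 21% at a median split and 10% with the top fifth as exposed. Those are fixed control quantiles on an exactly linear logit, so that score would normally stay continuous. The Youden PAR for it averaged 21%, the same as the median split. The spread shows that any choice of reference group moves a PAR; it is not evidence against Youden.

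**The remedy is not perfectly clean.** Keeping a quadratic term after the same linearity pre-test gave 7.0-7.2% overall. At a flag of 0.05 that is close to a fixed-direction Youden cut (7.0%); at 0.20 it is better than Youden (11-16%). Tertiles after the flag gave 5.2-5.6%. Part of the inflation belongs to the pre-test.

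**The article is a condensation.** The full protocol and the PRS method are in supplementary files not seen here and may settle how the PRS is grouped. They do not remove the objection to a rule that the article states outright and that an analysis plan following it would inherit.

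**Conclusion.** The point holds for covariates to which the Youden option is applied in the same data: about 26-28% type I error with direction fixed and 44-45% with direction free, against 5%, and a spurious PAR of about 5-7%. Across all null covariates, with Youden used only after a linearity flag, the error is about 7-16%. The first pair of rates is distribution-free. The second range assumes a normal covariate, a quadratic flag at 0.05 to 0.20, and Youden as the option always taken once flagged. For strong established risk factors the consequence is mainly an optimistic OR and PAR, whose size depends on curve shapes the documents do not give.

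Harm is possible, not certain, because the choice among the three sources is left open. The clause should still be changed before the outcome data are analysed: it brings no inferential gain, and the article already names alternatives that hold the error much closer to 5%.

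**What to change.** - Delete the ROC/Youden option, or allow only a cut found in separate data.
- When linearity fails, keep the covariate continuous with the fractional polynomial already fitted or a spline. Otherwise use cut-offs fixed without reference to case status (literature cut-offs or tertiles), in a stated order of preference that replaces the open choice.
- If the PAR needs PRS categories, fix them before the outcome data are examined. The number of groups and the reference are the sponsor's choice, and the full documents may already set them.

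**Cost.** Wording only; no new data or recruitment. A non-linear effect is reported as a curve or a contrast between chosen values instead of a single OR. Pre-testing linearity still leaves a small residual inflation (7.0-7.2% in the check above with a quadratic term).

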### Sample size calculation

We applied the following statistical assumptions: odds ratio for genetics was set at 1.3, allele frequency of 10%, inheritance model was dominant (since the presence of only one polymorphic allele is required to the risk calculation), the prevalence of CVD in the general population of 10%, statistical power of 90%, type I error rate (α) of 0.05, 2-sided significance tests, resulting in a sample of 1,867 cases and 1,867 controls. Sample size calculation was performed using Quanto Software Version 1.2.4.

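### A covariate cut at the Youden point of the study's own cases and controls and then tested at 5% gives about 27% to 50% false positives if it is null; the rule should be dropped

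*Protocol article*

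**What the plan says.** The relevant rule is in the protocol article under *Quantitative variables and statistical analysis*. Linearity on the logit is examined with smoothed scatter plots and fractional polynomials. A covariate that fails is categorised for the logistic regression by one of three routes: literature cut-offs, tertiles, or an "optimal cut-off obtained from the Receiver Operating Characteristic (ROC) curve, whichever is deemed most appropriate". For the third route the criterion is explicit: "it will be defined as the one that maximizes the Youden index".

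The resulting variable is judged by the general rule under *Estimation of population attributable risk*: "All hypothesis tests will be 2-sided and p-value<0.05 considered statistically significant". Under *Variables*, an attributable risk is then calculated for each variable whose odds ratio is significantly raised, and the polygenic risk score (PRS) is named among them.

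Literature cut-offs are a separate route, so the ROC cut-off would come from the study's own cases and controls. The article mentions no split sample, resampling or corrected p-value for it.

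**The concern.** The Youden index is sensitivity + specificity - 1, which is the case-control difference in the proportion above the cut. Choosing the cut that maximises it is choosing the largest such difference in the data. An ordinary p-value and confidence interval then treat a maximum over thousands of candidate cuts as one prespecified comparison.

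Two features add to this. The linearity check itself relates the covariate to case status, so the choice among the three routes is made after the outcome has been seen. Significance is also the gate to an attributable risk, and the Introduction gives attributable fractions as the purpose of the study. A covariate with no association could be declared a risk factor and be given an attributable risk. An OR estimated at the maximising cut is biased away from 1.

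This is separate from the information lost by categorising. It is also not a detail left to an analysis plan, because the article itself names the method, the criterion and the discretion.

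**Working it through.** **1. The plan's own figure.** Inputs under *Sample size calculation*: "odds ratio for genetics was set at 1.3", "allele frequency of 10%, inheritance model was dominant", "the prevalence of CVD in the general population of 10"%, "statistical power of 90"%, "type I error rate (α) of 0.05, 2-sided significance tests".

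- Carrier frequency: 1 - 0.9² = 0.19.
- Risks r0 (non-carriers) and r1 (carriers) solve 0.81·r0 + 0.19·r1 = 0.10 with OR 1.3, giving r0 = 0.0952 and r1 = 0.1204.
- Carriers among cases: 0.19 × 0.1204 / 0.10 = 0.2287. Among controls: 0.19 × 0.8796 / 0.90 = 0.1857.
- n = [1.960·√(2·0.2072·0.7928) + 1.282·√(0.2287·0.7713 + 0.1857·0.8143)]² / 0.0430² ≈ 1,868 per group (unrounded inputs). The likelihood-ratio version gives 1,867.

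The stated 1,867 + 1,867 reproduces and is not in dispute. It is the size used below.

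**2. A bound without simulation.** Let J be the Youden index and p the proportion above the cut. The 1-df statistic is J² / [p(1-p)·2/n]. Since p(1-p) ≤ 0.25, any J above 1.96·√(0.25·2/1867) = 0.0321 is significant at 5%, wherever the cut falls. Under no association, the large-sample (Smirnov) result is P(max J > j) ≈ exp(-n·j²), and n·j² = 1.96²/2 = 1.92. So at least exp(-1.92) ≈ 15% of null covariates are significant with the direction fixed. With the direction free, the bound is about 2·exp(-1.92) - 2·exp(-4·1.92) ≈ 29%.

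**3. Simulation under no association.** There were 10,000 to 20,000 data sets of 1,867 + 1,867 per setting, with the cut at the maximum of J and an ordinary chi-square test at two-sided 0.05. 'Fixed' means that higher values are taken as the risk direction; 'free' means that the direction is also read from the data.

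| Setting | Fixed | Free |
|---|---|---|
| Youden cut, all data sets | 27% | 44-45% |
| Youden cut after a failed quadratic check (p<0.05) | 48-52% | 69-76% |
| Youden cut after a failed first-degree fractional polynomial check | 37-50% | 61-86% |
| Cuts limited to the central 80% of the data | 22% | 43% |
| Cuts limited to the central 50% | 16% | 32% |

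Two comparators keep the nominal level: a median split gives 4.5-4.9% and the linear term 4.9%. Ranges within a cell cover normal and lognormal covariates.

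**4. The whole procedure.** Suppose that the Youden cut is used only after a failed 5% quadratic check and a linear term otherwise. For a normal covariate the check fails in 5.1% of null data sets:

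- Fixed: 0.051 × 0.525 + 0.949 × 0.049 ≈ 0.073 (simulated 0.074).
- Free: 0.051 × 0.755 + 0.949 × 0.049 ≈ 0.085 (simulated 0.086).

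Across the distributions and checks tried, the range is about 5-9% per covariate. If failure is declared more readily, for example from plots, the rate moves towards the first row of the table.

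**5. Size of the estimates.** Attributable risk is taken as (proportion exposed among cases) × (1 - 1/OR).

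- No association, free direction: median OR 1.15, 95th percentile 1.30, which equals the design OR. Median attributable risk is about 6%, 95th percentile about 16%.
- Real effect, fixed direction, 1,500 data sets each, estimated OR against true OR at the chosen cut: see below.

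| True effect | Median OR inflation | 95% CI coverage |
|---|---|---|
| Step at upper tertile, OR 1.3 | 4.8% | 90% |
| Step, OR 1.5 | 3.2% | 93% |
| Step, OR 2.0 | 2.0% | 94% |
| Linear, OR 1.3 per SD | 6% | 88% |

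**The case against.** The strongest reply is that the plan does not cut every covariate at the Youden point. The cut needs a failed linearity check and is one of three routes, two of which take their cut-offs without reference to the outcome. A reader might infer that the plan as a whole has a false-positive rate of 27-50%. The article does not support that: with a formal 5% check the rate is about 5-9% per covariate. This part of the reply stands. It is weakened only because the article sets no threshold for the check and also relies on plots, so the trigger rate is not fixed.

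The null case may also be a poor description of this study. Most listed covariates are established risk factors, several may be recorded as categories and so never face a linearity check, and the PRS uses only variants already linked to cardiovascular risk. With a real effect the bias is modest, as step 5 shows. That stands too.

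A reader might judge the bias by the OR among falsely significant covariates, with a median of about 1.21. Most of that is selection on significance, since a median split chosen without the outcome gives about 1.16 among its own false positives. Only the difference, about 0.05, belongs to the Youden cut.

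Finally, a reader might assume that the PRS will be cut this way. The wording permits it, but how the PRS is calculated is deferred to S3 File, which is not shown, so this cannot be settled.

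**Conclusion.** The concern holds for any covariate that is actually cut at the Youden point of the study data. If that covariate is unrelated to disease, the nominal 5% test rejects in about 26-27% of studies (direction fixed), about 50% after a failed quadratic check, and about 44% when the direction is also taken from the data. Every Youden setting examined was at least three times nominal. The OR, and any attributable risk calculated because it is significant, is biased away from the null, clearly so when there is no effect and slightly when there is one.

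The figures assume a normal or lognormal covariate, a quadratic or first-degree fractional polynomial check at 5%, and univariate tests. The size in the adjusted multiple regression was not computed, nor was the extra effect of choosing among the three routes after seeing the data. This should be changed, but it does not invalidate the study or its sample size.

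**What to change.** Delete the ROC/Youden route and the clause that leaves the choice of route to judgement. When linearity fails, either:

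- keep the fractional polynomial that the plan already fits to check linearity, or use splines; or
- categorise at literature cut-offs or at quantiles of the control distribution, fixed for each variable before case-control data are analysed.

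State the criterion by which linearity is judged to fail. If a Youden cut is still wanted, present it as descriptive, with no p-value and no attributable risk, or correct its p-value, OR and attributable risk by resampling the whole cut-selection step.

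The cost is a wording change, with no effect on recruitment, data or sample size. Some covariates will show a less striking OR, and a curve is slightly harder to present than a single cut.

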#### Estimation of population attributable risk

To characterize the study population, categorical variables will be described as counts and proportions and compared with Pearson’s chi-square test or with Fisher’s exact test [41]. Normally and asymmetrically distributed quantitative variables will be expressed as mean (standard deviation) or median (interquartile range), respectively [42]. Normality will be assessed by visually inspecting histograms and applying normality tests, if appropriate [43, 44]. Comparison of these continuous type variables will be carried out with Student’s t test for independent samples or Mann-Whitney test for non-parametric distribution [41].

All statistical analyses will follow the complete case analysis principle. All hypothesis tests will be 2-sided and p-value<0.05 considered statistically significant. Statistical data analysis will be conducted with SAS 9.4 (SAS Institute, Cary, NC).

#### Bias control

Eligibility criteria for cases and controls will be strictly followed to reduce selection bias. The criteria defined for the first ASCVD event were standardized, and all sites have been trained for the correct identification, data recording, and reporting of information. Cases will be validated by the adjudication committee through clinical data, diagnostic tests, hospitalization and/or discharge summary, among others, using the standardized and validated process for diagnoses [45, 46]. The relationship between the variables will be adjusted by multivariate logistic models. Data monitoring will be applied throughout the entire study timeline to assure data quality. Blood and urine samples collection have been standardized, and genetic and biochemistry analyses will be performed in a core lab to guarantee the standardization of methods and quality control.

